### Sample size calculation and statistical analyses

The number of patients required to provide sufficient power to test the first objective of the proposed study was derived from a power analysis based on a small expected between-group effect size of .20, as measured with Cohen’s *d*. With alpha = 0.05 and power = 0.85 (two-sided test), 900 patients are needed (i.e., 450 in each group). The data will be analysed according to the intention-to-treat principle, with the inclusion of all randomised patients in the statistical analysis regardless of whether they completed the study.

Univariable and multivariable linear and logistic regression analyses will be performed to examine the group effects on health status, device acceptance and satisfaction with care at several points in time. Analysis of (co)variance with repeated measures will be performed to assess between-group differences in changes in these patient-reported outcomes over 2 years.

Patients’ answers on the ‘Satisfaction with remote monitoring’ questionnaire will be used to classify them into subgroups of patients that are/are not satisfied with remote monitoring. Chi-square tests and Student’s t-tests (or a non-parametric equivalent if necessary) will be performed to explore the demographic, clinical, and psychological characteristics of the patients in these subgroups. Also, multivariable logistic and linear regression analyses will be performed to examine which factors are independently associated with satisfaction with remote monitoring as a dichotomous outcome (satisfied: yes/no) and as a continuous outcome (satisfaction visual analogue scale 0–10), respectively.

To determine the cost-effectiveness, both short-term and long-term country-specific cost-effectiveness analyses will be performed. The short-term analysis has a 2-year time horizon, while the long-term analysis will have a lifetime horizon. Data used for the short-term analysis will be based on the data captured during the trial, while data used for the long-term analysis will consist of a combination of trial data and data from other sources. These data will be combined using a disease progression and treatment model and will be analysed using probabilistic analyses, sensitivity analyses, and scenario analyses. The primary cost-effectiveness outcome will be the incremental cost per quality-adjusted life year (QALY) gained.

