### Study population

Consecutive patients receiving an ICD or CRT-defibrillator (CRT-D) at one of the participating centres will be screened for study participation. Patients implanted with a first-time (primary or secondary prophylactic) ICD or CRT-D compatible with the LATITUDE® Patient Management system from Boston Scientific, with left ventricular ejection fraction ≤35 % and symptomatic heart failure (New York Heart Association functional class II or III) at the time of implantation, and providing written informed consent will be eligible to participate. Patients will be excluded if they are younger than 18 or older than 85 years of age, on the waiting list for heart transplantation, have a history of psychiatric illness other than affective/anxiety disorders, or are unable to complete the questionnaires due to cognitive impairments or insufficient knowledge of the language.

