### Study procedure, randomisation and follow-up

When scheduled for device implantation, eligible patients receive a letter describing the purpose, design and possible benefits/risks of the study. Patients willing to participate are asked to sign an informed consent form. Of note, study refusal or withdrawal due to the patient having a strong preference for remote monitoring or in-clinic follow-up will be registered.

At discharge from hospital after implantation, included patients receive the baseline questionnaire and are asked to complete this 1 to 2 weeks after implantation (T_0_) to avoid measuring preoperative distress. When the completed T_0_ questionnaire is received at Tilburg University–which serves as core lab for the patient-reported outcomes–patients are randomised in a 1:1 fashion to either remote patient monitoring + in-clinic follow-up (RPM group) or in-clinic follow-up only (In-Clinic group) with the use of a blocked randomisation procedure. To ensure that the relative percentage of ICD and CRT-D patients is equal in both groups, we use separate randomisation procedures within these two subsets of patients.

Four to 8 weeks after implantation (preferably during the first in-clinic visit for assessment of wound healing etc.), patients in the RPM group will receive the remote monitoring system and be instructed how to install and use it. In accordance with the ACC/AHA/HRS guidelines, patients randomised to this group will visit the outpatient clinic again at 12 and 24 months after implantation [2]. The intermediate check-ups will be performed remotely. Patients randomised to the In-Clinic group will be followed up according to standard practice at the participating centres and visit the outpatient clinic (at least) every 3–6 months during the study. For patients in both groups, the follow-up assessments will take place at 3 (T_1_), 6 (T_2_), 12 (T_3_), and 24 (T_4_) months post-implantation. A schematic representation of the study design is shown in Fig. 1.

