Information on clinical characteristics and outcomes, including disease status, comorbidities, use of cardiac and psychotropic medication, ventricular arrhythmias, appropriate and inappropriate ICD therapy, in-clinic visits, hospital admissions, and mortality will be obtained from patients’ medical records or through device interrogation and gathered via electronic case report forms (Research Online) at baseline (T_0_), 6 (T_2_), 12 (T_3_) and 24 (T_4_) months after implantation.

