## Discussion

Large-scale trials have shown that remote patient monitoring is a safe, effective and timely alternative for conventional in-clinic follow-up of ICD/CRT-D patients [6]. However, these trials have fallen short in their patient-centredness and have left an important question unanswered: namely, what do patients think about remote monitoring [12]? To date, evidence on the patient perspective on remote monitoring is scarce and inconsistent. As emphasised in a recent scientific statement from the American Heart Association, the assessment of patient-reported outcomes such as patient-reported health status is essential to enhance the patient-centredness of care and better characterise the impact of healthcare delivery on patient health [26]. No study has examined whether there is a subset of patients who might not benefit from remote monitoring in terms of patient-reported outcomes and would be more satisfied with standard clinical follow-up visits, and whether they are distinguishable based on their demographic, clinical, or psychological profile. The REMOTE-CIED study is an international, prospective randomised controlled study specifically designed to provide more insight into the patient perspective on and cost-effectiveness of remote monitoring compared with in-clinic follow-up in ICD/CRT-D patients. This study will be able to show how patients feel about remote monitoring and determine whether there are subgroups of patients that might be better served by receiving in-clinic follow-up visits. The study aims to include 900 consecutive patients from five European countries, who will be followed-up for 2 years post-implantation.

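### The 900 patients are exactly the complete-data number for one unadjusted comparison and also the recruitment target, so the stated 85% power makes no allowance for death or unreturned questionnaires

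*Protocol article*

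**What the plan says.** The sample size paragraph of the protocol article (Methods, Sample size calculation and statistical analyses) bases the number on a "small expected between-group effect size of .20" in Cohen's d and concludes: "With alpha = 0.05 and power = 0.85 (two-sided test), 900 patients are needed (i.e., 450 in each group". It ties this to the first objective, the comparison of patient-reported outcomes. It names no time point, expected loss or inflation.

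The number to recruit is the same. The Discussion says: "The study aims to include 900 consecutive patients from five European countries, who will be followed-up for 2 years post-implantation". The Abstract also gives 900.

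Other sections show that loss is expected:

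- Patients have an ejection fraction of at most 35% and "symptomatic heart failure (New York Heart Association functional class II or III) at the time of implantation" (Study population).
- On questionnaires, "the follow-up assessments will take place at 3 (T_1_), 6 (T_2_), 12 (T_3_), and 24 (T_4_) months post-implantation" (Study procedure, randomisation and follow-up).
- Among the clinical data, "hospital admissions, and mortality will be obtained from patients’ medical records or through device interrogation" (Measures).
- The intention-to-treat sentence reads "with the inclusion of all randomised patients in the statistical analysis regardless of whether they completed the study" (Sample size calculation and statistical analyses), so non-completers are anticipated.

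**The concern.** The three primary endpoints (health status, device acceptance and satisfaction with care) are questionnaire scores. A patient who dies or stops replying gives no later score. If the number of patients with scores that the test needs equals the number recruited, every lost score takes power below the stated value. The intention-to-treat rule decides who belongs to the analysis set. It does not supply scores that were never given, and imputation does not recover the lost information in full.

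The expected effect is small, so a non-significant result is quite possible. A reader would then take it as evidence against a difference of d = 0.20 from a trial with 85% power. If a material share of scores is missing and the analysis is unadjusted, that reading gives the result more weight than it can bear.

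**Working it through.** **Inputs from the article.** d = 0.20 (so SD = 1 on the standardised scale), two-sided alpha 0.05, power 0.85 and 450 per arm, all from the sample size paragraph. Allocation is equal ("patients are randomised in a 1:1 fashion", Study procedure, randomisation and follow-up).

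**Inputs assumed here.** The loss rate L, and the correlation r between baseline and follow-up scores. The article gives neither, so ranges are shown.

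**Step 1: reproduce the 900.** The normal approximation is

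n per arm = 2 (z₀.₉₇₅ + z₀.₈₅)² / d² = 2 (1.960 + 1.036)² / 0.04 = 448.9, rounded up to 449.

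The exact two-sample t-test (noncentral t) gives 449.88, rounded up to 450 per arm and 900 in total. Power at 450 per arm is 0.8501. Near alternatives do not give 450: 80% power needs 393 per arm, 90% power needs 526, and a one-sided test needs 360. The stated number is therefore the complete-data t-test number, with a reserve of 450 − 449.88 = 0.12 patients per arm.

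**Step 2: compare with the recruitment target.** Number needed = 900 and number to include = 900, so the implied allowance for loss is zero.

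**Step 3: unadjusted power after loss.** Evaluable n per arm = 450 (1 − L), d = 0.20, two-sided t-test:

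| Assumed loss L | n per arm | Power |
|---|---|---|
| 0% | 450 | 0.850 |
| 5% | 427.5 | 0.832 |
| 10% | 405 | 0.811 |
| 15% | 382.5 | 0.789 |
| 20% | 360 | 0.764 |
| 25% | 337.5 | 0.737 |
| 30% | 315 | 0.708 |

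Power of 80% needs about 393 per arm, so it is lost once L exceeds about 1 − 393/450 = 12.7%. With 20% loss (360 per arm), the smallest effect with 85% power is d = 0.224.

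**Step 4: what adjustment for the baseline score could give back.** Adjustment reduces the residual SD to about √(1 − r²), so the effective effect size is d / √(1 − r²). For r = 0.5 this is 0.20 / √0.75 = 0.231; for r = 0.4 it is 0.20 / √0.84 = 0.218.

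| Assumed r | Loss 10% | Loss 20% | Loss 25% |
|---|---|---|---|
| 0 | 0.811 | 0.764 | 0.737 |
| 0.4 | 0.873 | 0.832 | 0.808 |
| 0.5 | 0.907 | 0.872 | 0.850 |

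The loss is fully offset when 1 − r² = 1 − L, that is r = √L: about 0.32 for 10% loss, 0.45 for 20% and 0.55 for 30%.

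**Step 5: inflation, for comparison.** To keep 450 per arm evaluable, randomise 450 / (1 − L) per arm: 500 per arm (1000 in total) at 10% loss, and 562.5, rounded up to 563 per arm (1126 in total), at 20%.

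**The case against.** The strongest objection is that the planned analysis is richer than the t-test behind the 900. The article also plans multivariable regression and repeated-measures analysis of (co)variance, and all three primary instruments are completed at baseline and at every follow-up. Step 4 shows that a moderate baseline correlation would restore 85% power under substantial loss. This stands, and it rules out a tempting stronger reading: that 85% power holds only if nobody dies or stops replying. That is true of the unadjusted comparison (which the planned univariable regression also makes), but not of every planned analysis. Even so, the article states no correlation, does not say that baseline is the covariate, and does not derive the 900 from either.

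A reader might also infer that the trial lacks its stated power at 24 months. The article does not support so flat a claim. It attaches the 85% to no time point, plans comparisons at several times, and gives no loss rate. Loss at 3 or 6 months should be smaller, and 5% loss still leaves 0.83.

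Two further points stand. Refusal before randomisation costs no power, and patients are randomised only after the baseline questionnaire has been returned, so those who never respond do not enter the arms. Neither removes death or later non-return. And nothing has been miscalculated: the 900 reproduces exactly, and what is missing is an assumption about loss.

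One objection does not stand: that the full protocol or analysis plan may hold the allowance. Handling of missing scores can be left to those documents, but an inflation cannot sit there unseen, because the number needed and the number to include are both printed as 900.

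**Conclusion.** The concern holds in this form: the stated 85% power is the complete-data power of one unadjusted comparison, and the recruitment target adds nothing for the deaths and non-return that the article itself foresees. For that comparison power drops to 0.81, 0.76 and 0.71 at assumed losses of 10%, 20% and 30%. Whether the analyses actually run will have less than 85% power cannot be settled from the article. It depends on the time point, the true loss and the correlation with baseline, none of which the calculation specifies. The figures assume equal loss in both arms and an unchanged true difference of d = 0.20 among patients with scores.

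**What to change.** Keep 900 and correct the statement, in one of two ways.

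1. Name the time point and the expected loss, and give the power after loss. For example: 450 per arm gives 85% power for d = 0.20 with complete data; with 20% of scores missing at 24 months, unadjusted power is 76%, and 85% power is reached for d = 0.224.
2. Base the 85% on the planned analysis with the baseline score as covariate, and state the assumed correlation and its source. For example, r = 0.5 gives 87% power with 20% loss and 85% with 25% loss; r = 0.4 gives 83% with 20% loss. The less favourable case should be shown as well.

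Either costs about one sentence and no extra patients. Under the first, the stated figure becomes somewhat less favourable. Under the second, the claim depends on a correlation that has to be justified. Inflating recruitment as in step 5 is possible but not needed to make the statement accurate.

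### The named primary analyses, in their standard form, leave out randomised patients with missing scores, although the plan promises to analyse all of them

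*Protocol article*

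**What the plan says.** All of the analysis text is in the protocol article, Methods, 'Sample size calculation and statistical analyses'.

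- **Analysis set.** Intention-to-treat, "with the inclusion of all randomised patients in the statistical analysis regardless of whether they completed the study".
- **Analysis at visits.** "Univariable and multivariable linear and logistic regression analyses will be performed to examine the group effects". This covers all three primary endpoints and more than one follow-up time.
- **Analysis of change.** "Analysis of (co)variance with repeated measures will be performed to assess between-group differences in changes in these patient-reported outcomes over 2 years".
- **Sample size.** Based on a "small expected between-group effect size of .20": "With alpha = 0.05 and power = 0.85 (two-sided test), 900 patients are needed (i.e., 450 in each group").

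Under 'Study procedure, randomisation and follow-up', allocation follows receipt of the completed T0 questionnaire, and "follow-up assessments will take place at 3 (T_1_), 6 (T_2_), 12 (T_3_), and 24 (T_4_) months post-implantation". The same section says that "study refusal or withdrawal due to the patient having a strong preference for remote monitoring or in-clinic follow-up will be registered". The 'Measures' section lists mortality among the outcomes collected. The article names no mixed model, no imputation and no rule for scores after death.

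**The concern.** The article fixes the analysis set and then names methods that, as ordinarily run, do not use that set. A patient who answers T1, T2 and T3 but not T4 drops out of a classical repeated-measures AN(C)OVA altogether. A patient who misses T4 drops out of the 24-month regression. What would be reported as an analysis of all randomised patients could in practice be one of completers or respondents.

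Two things are at stake. The first is precision, because the sample size has no reserve for lost scores. The second is validity. If patients with poor scores leave one arm more readily than the other, those who remain are no longer comparable. Loss of this kind is plausible here: the patients have symptomatic heart failure and are followed for two years, and the sponsor thought preference-driven withdrawal worth recording. Such a preference may well be related to satisfaction with care, which is a primary endpoint.

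**Working it through.** **1. The plan's own sample size.** Inputs from the article: d = 0.20, two-sided alpha 0.05, power 0.85, 1:1 allocation.

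n per arm = 2 × (1.960 + 1.036)² / 0.20² = 448.9, so 449 per arm (898 in total). The t-test version gives 449.9, so 450 per arm and 900 in total. The stated figure reproduces. It is the number needed with complete scores and contains no allowance for loss.

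**2. Share with complete records.** T0 is present for everyone randomised, so only T1–T4 can be missing. With an assumed new loss of m per wave, the complete share is (1 − m)⁴:

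- m = 0.05: 0.95⁴ = 0.815, or 733 of 900
- m = 0.10: 0.90⁴ = 0.656, or 590 of 900

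**3. Power if only patients with scores are analysed.** Power = Φ(0.20 × √(n/2) − 1.960), with n per arm = 450 × (1 − loss). The loss rates are assumed.

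| Loss | n per arm | 0.20 × √(n/2) | Power |
|---|---|---|---|
| 0% | 450 | 3.000 | 85.1% |
| 10% | 405 | 2.846 | 81.2% |
| 20% | 360 | 2.683 | 76.5% |
| 30% | 315 | 2.510 | 70.9% |

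**4. Can a false difference arise?** This was simulated with 450 per arm, five assessments, correlation 0.6 between assessments, SD 1, no true group effect and 1,500 replicates. Loss is permanent, with logit of the chance of leaving before the next visit = −2.6 − b × last score. In the remote-monitoring arm b = 0.7 or 1.0, so low scorers leave; in the In-Clinic arm b = 0. By 24 months about 25% are lost in the In-Clinic arm and 28–32% in the remote-monitoring arm. All of these settings are assumptions.

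| Contrast at 24 months | Bias, b = 0.7 | Bias, b = 1.0 |
|---|---|---|
| Respondents, unadjusted | +0.13 SD | +0.19 SD |
| Respondents, adjusted for baseline | +0.04 SD | +0.06 SD |
| Completers, change T0 to T4 | −0.02 SD | −0.03 SD |
| All randomised, likelihood-type estimate | about 0 | about 0 |

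The false-positive rate at a nominal 5% is about 36–69% for the unadjusted regression and 9–15% for the adjusted one. The group-by-time test stays near nominal, at 6–7%. The group main effect of a completer repeated-measures ANOVA is biased by +0.14 to +0.21 SD, but that is not the contrast in the sentence on change.

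**5. Conditions.** With the same score-related loss in both arms (equal b and equal intercept), or loss unrelated to score (even 66% v 81% retained), every completer contrast has bias of about 0 and a false-positive rate of about 4–6%. The bias therefore needs score-related loss that differs by arm. The clean result for the likelihood-type estimate also depends on the set-up, because loss was made to depend only on observed scores.

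**The case against.** The strongest reply is that the article never specifies complete cases. It commits to the opposite, and the named analyses can honour that commitment if they follow multiple imputation or are fitted by likelihood. The choice between these is commonly left to the full protocol or the SAP, neither of which is shown. This stands as far as it goes. A reader might infer that the named methods can never give an intention-to-treat result, or that the primary result will be a completer analysis. The document supports neither inference. It supports only that the methods as named, in standard form, do not match the stated analysis set.

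A reader might also infer a bias about as large as the design effect of 0.20. That size belongs to the unadjusted 24-month comparison under one-sided, score-related loss. For the contrast in the quoted sentence, change over time, the bias is small and of opposite sign. The article also plans multivariable regression, where the bias is 0.04–0.06 SD if baseline is among the covariates.

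Nor does the article say that arm-specific withdrawal is expected. It says that refusal or withdrawal for preference will be registered, in the paragraph on consent, without a rate or an arm. Finally, the unequal spacing of visits might be read as a breach of sphericity. Spacing alone does not establish that, standard corrections exist, and nothing calculated here tests it.

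What remains is the mismatch between promise and methods. It is more than an omitted detail, because the article states both sides of it.

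**Conclusion.** The point holds as an inconsistency that should be resolved before analysis. It does not show that the trial's result will be biased.

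The firm part needs no assumption: standard repeated-measures AN(C)OVA and per-visit regression do not include every randomised patient, and 900 carries no reserve for lost scores. The loss of power, from 85% to about 71–81%, rests on assumed loss of 10–30%. The false difference rests on stronger assumptions: score-related loss differing by arm, 25–32% lost by 24 months, and correlation 0.6. The article gives no dropout, death or correlation figure, so it cannot show which scenario is nearest. The importance is moderate, and the correction is cheap.

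**What to change.** For the primary comparison, replace repeated-measures AN(C)OVA and the separate per-visit regressions with one likelihood-based linear mixed model per endpoint:

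- Outcomes: all available scores from T0 to T4, with the baseline mean constrained equal across groups.
- Terms: visit, group-by-visit after baseline, and device type (ICD or CRT-D, the randomisation strata).
- Covariance: unstructured across the five assessments.

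Taking T0 as an outcome matters. With T0 only as a covariate and T1–T4 as outcomes, patients lost before T1 (roughly 68–75 of 900 under the assumed loss model) would contribute nothing. Here they contribute through T0. Both the group difference at a visit and the difference in change can be read from this one model. An acceptable alternative is to keep the named analyses and apply them after multiple imputation.

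Two additions are needed. State how scores after death are treated, since a likelihood model otherwise handles them implicitly as missing at random. Add a sensitivity analysis that shifts the unobserved scores of patients registered as withdrawing for preference (delta adjustment) over a stated range.

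The cost is plan wording, some programming and modelling work, with no new data or patients. The price is reliance on a missing-at-random assumption, which the delta analysis is there to probe. The model recovers part of the precision lost to missing scores, not all of it.

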Recent surveys in the United States and Europe demonstrated that although the use of remote monitoring is growing, overall adaptation remains low and varies considerably between hospitals [8, 9]. Impediments to implementation include the absence of national guidelines and reimbursement models for remote monitoring in clinical practice [4, 6, 9–11]. Also, remote monitoring is unlikely to become the standard of care until it is conclusively demonstrated that patient outcome is favourably affected [12, 13]. Whether clinical effects of remote monitoring translate into improved patient-reported outcomes such as symptoms, quality of life and satisfaction with care, and whether patients are more satisfied with remote monitoring than in-clinic follow-up has received little attention.

To date, the few randomised controlled trials on remote monitoring in ICD patients that included patient-reported outcomes have yielded inconsistent results [14–16]. Prospective cohort studies using short ad hoc questionnaires have reported that 60–95 % of ICD patients are highly satisfied with remote monitoring and that it makes them feel safe [17–22]. However, these studies provided no information on how many patients refused to use a remote monitoring system and preferred to be checked at the outpatient clinic. This is essential, as a recent registry study from the United States showed that 24 % of the patients who received a remote monitoring system did not activate it [8].

No prospective randomised study has examined whether there is a subset of patients who might not benefit from remote monitoring in terms of patient-reported outcomes and might be more satisfied with standard clinical follow-up visits. For example, a substantial number of ICD patients report increased emotional distress, such as anxiety and depression [23]. The remote monitoring system might provide these patients with a sense of security, but on the other hand the system may act as a constant reminder of their device and underlying disease. Also, patients might miss the personal attention and reassurance from their treating physician and heart failure team [24]. A qualitative study on ICD patients who received a remote monitoring system showed that nonusers believed that in-clinic visits are psychologically advantageous and trusted the healthcare professionals over technology when it came to managing their health [25].

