The international REMOTE-CIED study is the first prospective, randomised controlled study primarily designed to examine the patient perspective on remote monitoring in ICD patients, in order to enhance the patient-centredness of care in this patient group. The primary study objective is to evaluate the influence of remote patient monitoring versus conventional in-clinic follow-up on patient-reported outcomes, by means of standardised and validated questionnaires. Secondary objectives are to (1) identify subgroups of patients who might not be satisfied with remote monitoring and examine if they are distinguishable based on their demographic, clinical, or psychological profile; and (2) investigate the cost-effectiveness of remote monitoring + in-clinic follow-up as compared with in-clinic follow-up only.

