### Measures

Primary endpoints are patient-reported heart failure-specific health status (i.e., symptoms, functioning and quality of life), ICD acceptance and satisfaction with care. To assess these patient-reported outcomes and potentially associated psychological factors (i.e., Type D personality, psychological distress), patients in both groups will complete a number of questionnaires at the five assessment times (Table 1). All questionnaires are standardised and validated, except for the questionnaires used to assess patient satisfaction with remote monitoring, and their productivity and healthcare utilisation for cost-effectiveness. For these purposes, new questionnaires were developed.

**Table 1 Tab1:** Patient-reported outcomes and psychological factors assessed in the study

Construct	Questionnaire	T_0_	T_1_	T_2_	T_3_	T_4_
Outcome measures						
Health status	Kansas City Cardiomyopathy Questionnaire (KCCQ)	x	x	x	x	x
Device acceptance	Florida Patient Acceptance Survey (FPAS)	x	x	x	x	x
Satisfaction with care	Visual analogue scale (0–100)	x	x	x	x	x
Satisfaction with remote monitoring^a^	Purpose-designed questionnaire		x	x	x	x
Cost-effectiveness: QALY	Euroqol 5D (EQ-5D) + VAS scale	x	x	x	x	x
Cost-effectiveness: productivity and health care utilisation	Purpose-designed questionnaire		x	x	x	x
Psychological variables						
ICD concerns	ICD Patient Concerns Questionnaire (ICDC)	x		x	x	x
ICD expectations^b^	Expectations regarding ICD	x				
Illness perception	Illness Perceptions Questionnaire (IPQ)	x			x	
Anxiety symptoms	Generalised Anxiety Disorder (GAD-7)	x			x	x
Depressive symptoms	Patient Health Questionnaire (PHQ-9)	x			x	x
Type D personality	Type D Scale (DS14)	x				
Self-care behaviour	European Heart Failure Self Care Behaviour Scale (EHFScBS)	x			x	x

T_0_ = Baseline; T_1_ = 3 months; T_2_ = 6 months; T_3_ = 12 months; T_4_ = 24 months

*ICD* implantable cardioverter defibrillator; *QALY* quality-adjusted life year; *VAS* visual analogue scale

^a^Patients in RPM group only

^b^Dutch patients only

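### The analysis of satisfaction within the remote monitoring arm answers the stated secondary objective, but cannot show which subgroups would do better with in-clinic follow-up, as the Discussion says the study will

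*Protocol article*

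**What the plan says.** All references are to the protocol article.

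- **Objective.** The Introduction words the first secondary objective as follows (last word omitted): "identify subgroups of patients who might not be satisfied with remote monitoring and examine if they are distinguishable based on their demographic, clinical, or psychological". This concerns remote monitoring alone.
- **Wider aim.** Earlier in the Introduction, the gap in knowledge is described as whether a subset of patients "might not benefit from remote monitoring in terms of patient-reported outcomes and might be more satisfied with standard clinical follow-up visits". The Discussion says the study will "determine whether there are subgroups of patients that might be better served by receiving in-clinic follow-up visits". Both statements are comparative.
- **Method.** Under Sample size calculation and statistical analyses, answers on the purpose-designed questionnaire "will be used to classify them into subgroups of patients that are/are not satisfied with remote monitoring". Chi-square and t-tests then serve "to explore the demographic, clinical, and psychological characteristics of the patients in these subgroups", and multivariable regressions serve "to examine which factors are independently associated with satisfaction with remote monitoring as a dichotomous outcome" and, in parallel, as a continuous score.
- **Who answers.** Table 1 schedules that questionnaire at T1 to T4, with the footnote "Patients in RPM group only".
- **Two-arm analyses.** The same section plans regressions "to examine the group effects on health status, device acceptance and satisfaction with care at several points in time", and repeated-measures analyses of change. No interaction between group and a baseline factor is stated.

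**The concern.** To say that a subgroup is better off with clinic visits is to say something about the difference between arms in that subgroup. The method given for the subgroup question contains only one arm. Its outcome does not exist in the In-Clinic group, so no term for randomised group can enter the model. The satisfied and dissatisfied classes are also formed after randomisation and have no In-Clinic counterpart.

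An association between a trait and dissatisfaction in the RPM arm therefore has two possible explanations that this analysis cannot separate. The trait may make remote monitoring in particular a poor fit, or it may go with lower satisfaction whatever the follow-up. The Introduction itself names anxious and depressed patients as possible poor candidates, and for them the second explanation is plausible. If RPM-only associations were read as the Discussion suggests, such patients could be steered towards clinic visits with no evidence that they fare better there.

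**Working it through.** **1. The plan's own figure.** Inputs from the sample size section: d = 0.20, two-sided alpha 0.05, power 0.85, 1:1 allocation.

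n per arm = 2 × (1.960 + 1.036)² / 0.20² = 449, or 898 in total. With 450 per arm, power is 0.851. The stated 900 reproduces. The section ties it to the first objective, the overall comparison of arms.

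**2. Aim against method.**

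| Question | Contrast needed | Contrast in the stated method |
|---|---|---|
| Who is not satisfied with remote monitoring? | Between patients within the RPM arm | The same: matched |
| Who would do better with clinic visits? | RPM minus In-Clinic, compared across levels of a baseline factor | None stated |

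A larger sample would not close the second gap, because the In-Clinic arm does not enter that analysis.

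**3. A factor that acts equally in both arms.** Assumed for illustration, since the article gives no such figure: a trait lowers satisfaction by 0.5 SD in each arm and is held by a share p of patients. The true interaction is 0.5 − 0.5 = 0. In 450 RPM patients the trait's SE is sqrt(1/(450p) + 1/(450(1 − p))).

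- p = 0.50: SE = 0.094, and 0.5/0.094 − 1.96 = 3.34, so power is over 99%.
- p = 0.25: SE = 0.109, and 0.5/0.109 − 1.96 = 2.63, so power is over 99%.

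The RPM-only analysis would almost always find the trait, although the choice of follow-up makes no difference to it.

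**4. What two-arm interactions could show.** Assumptions: all 900 analysed, outcome SD 1, binary factor with share p (not in the article), no gain from covariates.

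SE of interaction = sqrt(2/(450p) + 2/(450(1 − p))). Detectable at 80% power = 2.80 × SE. Power for 0.20 SD = Φ(0.20/SE − 1.96).

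| p | SE | Detectable at 80% power | Power for 0.20 SD |
|---|---|---|---|
| 0.50 | 0.133 | 0.37 SD | 32% |
| 0.25 | 0.154 | 0.43 SD | 25% |
| 0.20 | 0.167 | 0.47 SD | 22% |
| 0.10 | 0.222 | 0.62 SD | 15% |

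If 20% were lost (assumed, leaving 720), the first two detectable values become 0.42 and 0.48 SD.

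**5. Are the data there?** Table 1 has the satisfaction-with-care scale, KCCQ and FPAS at T0 to T4 with no restriction to one arm, and GAD-7, PHQ-9, DS14 and ICDC at T0. Under Study procedure, randomisation and follow-up, randomisation comes after the completed T0 questionnaire is received, so these factors precede allocation. Device type is known too, because randomisation is run separately for ICD and CRT-D patients.

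**The case against.** The strongest reply is that the formal objective and its analysis agree. Only patients who have remote monitoring can rate it, so restricting the questionnaire to the RPM group follows from the question. That stands: the RPM-only analysis is right for the objective as worded. The conflict is only with background text in the Introduction and one Discussion sentence, neither of which is an objective or a hypothesis. This lowers the weight of the point but does not remove it, because the Discussion sentence says what the study will determine.

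A second reply is that the article is condensed and that moderator analyses may sit in a document not shown. This is fair, and their absence from the article does not show that none are planned. The point rests instead on what the article does state: a specific one-arm method for the subgroup question, and a conclusion that this method cannot support.

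Third, interactions would be imprecise and numerous. Eight factors on three outcomes would make 24 tests, with 24 × 0.05 = 1.2 expected false positives if no interaction were real. That argues for a short list labelled exploratory, and against replacing the RPM-only analysis.

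A reader might also infer that the randomised comparison is thrown away. It is not: the two-arm analyses of health status, device acceptance and satisfaction with care serve the primary objective. Nor does the article say that any patient group will be declared unfit for remote monitoring; it describes the subgroup tests as exploring characteristics.

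**Conclusion.** The point holds as a mismatch of scope. The RPM-only analysis meets the formal secondary objective but gives no support to a conclusion about who would do better with in-clinic follow-up. That follows from the design of the analysis and needs no numerical assumption.

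A reader might go further and infer that the trial cannot answer the comparative question. The documents do not support this: the outcomes are measured in both arms and the candidate factors are recorded before randomisation. The shortfall is in the stated analysis.

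The answer available from these data would still be limited. For assumed factor shares of 50% and 25%, the detectable interaction is 0.37 and 0.43 SD, about twice the design effect of 0.20 SD. The share, full follow-up and unit SD are assumptions; losses or rarer factors make it worse, and covariate adjustment could improve it. The point is a worthwhile, inexpensive improvement to a secondary question and leaves the primary comparison untouched.

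**What to change.** 1. Keep the RPM-only analysis as the analysis of the first secondary objective.
2. Add a short pre-listed set of group-by-baseline-factor interactions to the two-arm model, for example device type and T0 GAD-7, PHQ-9, DS14 and ICDC. Take the satisfaction-with-care scale as the lead outcome, with KCCQ and FPAS as supportive.
3. Report RPM-minus-In-Clinic differences by factor level with 95% confidence intervals, label them exploratory, and do not read a non-significant interaction as evidence of no difference.
4. Base any statement that a subgroup would do better with in-clinic follow-up only on these interactions. If they are not added, limit the Discussion sentence to describing who is dissatisfied with remote monitoring.

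The cost is a few models on data already collected. The drawbacks are low precision and multiplicity: five factors give 5 × 0.05 = 0.25 expected false positives on the lead outcome if no interaction is real, and 15 × 0.05 = 0.75 across all three outcomes. Narrowing the sentence alone costs nothing, but leaves the comparative question unanswered.
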